**Comparison Group**

Participants in the control group will be provided with educational materials produced by the British Heart Foundation explaining blood pressure, blood pressure prevention and recommended lifestyle behaviours to maintain heart health.

# SAFETY REPORTING

## Definition of Adverse Event (AE)

Any untoward medical occurrence in a participant to whom exercise intervention has been administered, including occurrences which are not necessarily caused by or related to that intervention.

## Procedures for Recording Adverse Events

All AEs occurring during the trial / or until completion of the final study visit that are observed by the Investigator or reported by the participant, will be recorded on the CRF, whether or not attributed to the exercise intervention.

The following information will be recorded: description, date of onset and end date, severity, assessment of relatedness to exercise intervention, other suspect drug or device and action taken. Follow-up information should be provided as necessary.

The severity of events will be assessed on the following scale: 1 = mild, 2 = moderate, 3 = severe.

AEs considered related to the trial treatment as judged by a medically qualified investigator or the Sponsor will be followed either until resolution, or the event is considered stable.

It will be left to the Investigator’s clinical judgment to decide whether or not an AE is of sufficient severity to require the participant’s removal from treatment. A participant may also voluntarily withdraw from treatment due to what he or she perceives as an intolerable AE. If either of these occurs, the participant must undergo an end of trial assessment and be given appropriate care under medical supervision until symptoms cease, or the condition becomes stable.

## Definition of a Serious Adverse Event

A serious adverse event is any untoward medical occurrence that:

- results in death
- is life-threatening
- requires inpatient hospitalisation or prolongation of existing hospitalisation
- results in persistent or significant disability/incapacity
- consists of a congenital anomaly or birth defect.

Other ‘important medical events’ may also be considered serious if they jeopardise the participant or require an intervention to prevent one of the above consequences.

NOTE: The term "life-threatening" in the definition of "serious" refers to an event in which the participant was at risk of death at the time of the event; it does not refer to an event which hypothetically might have caused death if it were more severe.

## Reporting Procedures for Serious Adverse Events

Safety reporting will be from baseline to the 18 month follow up visit.

Adverse events may also be recorded by the participant using the trial telephone number or email. Participants will be directly asked about adverse events at each study visit.

A serious adverse event (SAE) occurring to a participant should be reported to the REC that gave a favourable opinion of the study where in the opinion of the Chief Investigator the event was ‘related’ (resulted from administration of any of the research procedures) and ‘unexpected’ in relation to those procedures. Reports of related and unexpected SAEs should be submitted within 15 working days of the Chief Investigator becoming aware of the event, using the HRA [report of serious adverse event](http://www.nres.npsa.nhs.uk/docs/forms/Safety_Report_Form_(non-CTIMPs).doc) form (see HRA website).

## Blood Draw and IV Placement

Common risks associated with phlebotomy or cannula insertion are pain during the procedure and bruising (with associated pain afterwards). These risks will be minimised by ensuring that all staff are fully trained in phlebotomy. Bruising after the event will also be reduced by promptly applying pressure on the puncture site after the needle/cannula is withdrawn. All participants will be fully informed about these risks in the Participant Information Leaflet. Though uncommon (<1%) the worry associated with taking blood may cause some participants to feel unwell or faint before, during or after the procedure. The risk associated with this will be reduced by having an adequately equipped facility for performing the procedure (see above) and having a staff member trained in basic life support. Although phlebotomy is a very safe procedure, it does create a puncture wound on the skin which may very rarely lead to infection around the puncture site. The risk of this will be minimised by ensuring strict hygiene during the procedure and by not recruiting participants who are at increased risk of infection. In the event that a participant reports symptoms of an infection (local redness, swelling, pain or discharge of pus) they should be referred to their GP or to A+E urgently.

Risk to Researchers/Other Staff: Taking blood carries a risk of needle stick injury to the phlebotomist, which in turn carries a risk of exposure to blood borne infections. This risk will be minimised by a) ensuring staff are adequately trained, b) ensuring staff have been vaccinated against, and show immunity to Hepatitis B and c) having a local policy for needle stick injury which describes the process of being assessed for and receiving post exposure prophylaxis.

## MRI

MRI is a safe and non-invasive technique with no known risk when appropriately supervised. It does not involve ionising radiation (X-rays). Potential participants with ferromagnetic objects in their bodies or with implanted devices which can be damaged by the MRI magnet will be excluded. All participants entering the scanner room are screened for such objects. Doctors who are Advanced Life Support trained will be available during scans and the site is fully equipped for resuscitation (including defibrillation) in the unlikely event of a medical emergency during scanning.

While most people do not experience discomfort in a MRI environment, the enclosed space of the scanner can potentially feel uncomfortable. Discomfort from lying still for a long period of time will be minimised with comfortable padding and positioning. People with a history of severe claustrophobia would be excluded from participation in the study. Participants will be informed of the possibility of dizziness in the information sheet, and by the operator before they go in the scanner. If the participant does experience dizziness, they may choose to temporarily halt the table movement, they may choose to continue into the centre of the scanner where sensations of dizziness start going away, or they may choose to stop all procedures and come out of the scanner (either temporarily or to withdraw from the study). Participants will be given a chance to see the scanner before the study starts. All participants would be introduced carefully to the scanner and allowed to leave at any stage, should they wish to do so. Once in the scanner, participants would be able to indicate immediately if they wish the scanning to cease by squeezing a bulb placed in their hands, or by verbal request. As the MRI scanner is noisy, participants will be provided with ear plugs and protective headphones to reduce noise and aid communication between them and the investigators. It is important that these are fitted correctly to protect participant’s ears.

## Exercise Training

Exercise training is safe and the established global benefits to health and well-being outweigh negative complications and risks. However, risk of injury, medical complications and serious adverse events are reported in association with exercise participation. Muscle and joint soreness and minor musculoskeletal are common adverse effects of exercise training, however the risk of a serious adverse event including sudden cardiac death or non-fatal cardiac event is reported as below 0.01 per 10000 hours of participation. The following injuries and medical complications may be expected in association with exercise training:

| Accidental Injury | Fall (resulting in admission)  Head injury (resulting in admission)  Road traffic or pedestrian injury |
| --- | --- |
| Allergy | Insect bite  Seasonal allergy exposure |
| Cardiovascular | Exertional Hypotension  Tachycardia  Arrhythmia  Bradycardia  Sudden cardiac event and death |
| Dermatological | Abrasions and Blisters  Dry skin  Fungal infection |
| Gastro-intestinal | Dehydration  Irritable bowel  Increased bowel frequency  Gastro-intestinal blood loss  Gastrosphageal reflux |
| Gynaecology | Irregular menstrual cycle |
| Musculoskeletal | Muscle soreness  Muscle injury  Muscle cramps  Joint injury including sprain  Tendon injury or strain  Ligament tears  Joint inflammation or swelling  Fracture |
| Neurological | Back pain  Nerve entrapment  Headache  Pain |
| Renal | Haematuria  Proteinuria  Exercise associated hyponatraemia |
| Respiratory | Upper respiratory tract infection or viral illness  Exercise induced broncho-spasm |
| Thermal | Heat Cramps  Hyperthermia, Heat exhaustion if exercising in hot/humid environments  Heatstroke  Hypothermia if exercising in cold environments |

Participants shall report adverse events through either hard-copy or secure, computer-based reporting forms. All participants will be briefed to directly seek appropriate clinical care as needed for any adverse events.

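### The safety sections conflict on whose adverse events count, whether a listed exercise-related death goes to the ethics committee, and when reporting ends

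*Supplement*

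**What the plan says.** Protocol version 3.1, chapter 10 (Safety Reporting):

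- **10.1, AE definition.** "Any untoward medical occurrence in a participant to whom exercise intervention has been administered".
- **10.2, recording.** The rule covers "All AEs occurring during the trial / or until completion of the final study visit". Events go on the CRF whatever their attribution.
- **10.3, SAE definition.** "A serious adverse event is any untoward medical occurrence that" meets one of the listed criteria. The definition has no restriction to an arm or to exercise.
- **10.4, reporting.** "Safety reporting will be from baseline to the 18 month follow up visit". "Participants will be directly asked about adverse events at each study visit". An SAE in any participant goes to the REC if the Chief Investigator judges it both related to a research procedure and unexpected for that procedure. The deadline is: "Reports of related and unexpected SAEs should be submitted within 15 working days of the Chief Investigator becoming aware of the event".
- **10.7, Exercise Training.** A table is introduced with "The following injuries and medical complications may be expected in association with exercise training". Its cardiovascular row includes "Sudden cardiac event and death". Its accidental-injury row includes falls and head injuries that lead to hospital admission.

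Elsewhere, Trial Design and section 8.6 place the last scheduled visit at 52 weeks (plus or minus 2), followed only by an optional exit interview. Section 8.4 places randomisation after the baseline measures.

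**The concern.** Each conflict has its own consequence if staff follow the text literally.

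- **AE definition.** Controls have the same exercise tests and blood sampling as the exercise arm, and 50 of them are in the MRI subgroup. If their non-serious events are not AEs, a table by arm shows an excess under exercise that partly or wholly reflects the definition. The trial is open, so leaving the choice to staff who know the allocation does not remove the problem.
- **Expectedness.** The prompt REC report is the route by which a body outside the trial team learns of a grave related event. If a sudden death on the section 10.7 list counts as expected, that report is no longer required.
- **Window.** Staff cannot tell from the text whether safety reporting ends at the 52-week visit or about half a year later.

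**Working it through.** The plan gives no design figure to reproduce here. The check sets the sections side by side, with one date calculation.

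**1. Whose events count**

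| Section | Population | Start |
| --- | --- | --- |
| 10.1 AE definition | Those given exercise | When exercise has been given |
| 10.2 AE recording | All AEs, so it inherits 10.1 | Not separately stated |
| 10.3 SAE definition | No restriction | Not stated |
| 10.4 SAE reporting and AE questioning | Any participant | Baseline |

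Randomisation follows the baseline measures, so nobody in either arm has received the intervention at the baseline exercise test, cannulation or MRI. Under 10.1, non-serious events at that visit are not AEs, although 10.4 starts safety reporting there. After randomisation, 10.1 excludes the control arm: planned 100 of 200 participants.

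The two omissions differ. Losing baseline events in both arms loses information but does not itself bias the comparison of arms. Losing control events after randomisation does. Suppose a shared procedure, such as the 16-week exercise test, causes a non-serious event with the same probability *p* in each arm. The literal counts are then 100 × *p* under exercise and 0 under control, an apparent risk difference of *p* where the true difference is 0. The protocol gives no non-serious AE rate for both arms from which to put a number on *p*.

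**2. Whether a training-related sudden death triggers the REC report**

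- Section 10.4 needs both conditions: related and unexpected for the procedure.
- A training-related death meets the first.
- For the second, section 10.7 is the protocol's list of complications described as ones that may be expected with training, and it names sudden cardiac event and death.
- The list is not confined to minor effects. Injuries leading to admission meet the hospitalisation criterion in 10.3.
- Section 10.4 states no exception for fatal or life-threatening events.

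On that reading the second condition fails and no 15-working-day report is required. No other section clearly fills the gap. The annual review items for the Data Monitoring Committee (chapter 13) are recruitment, compliance, primary-outcome measurement and attrition, and the annual progress report to the REC (section 14.11) does not mention SAEs.

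**3. End of the reporting window**

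- 18 months = 18/12 × 52 = 78 weeks.
- From the 52-week visit: 78 − 52 = 26 weeks.
- From the latest date in that visit's window: 78 − (52 + 2) = 24 weeks.

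Section 10.4 therefore ends 24 to 26 weeks after the last scheduled visit, where section 10.2 stops. The text shown has no 18-month visit. The schedule figures in the appendices are not reproduced, so this was checked against the text only.

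**The case against.** The strongest defence is that the protocol is better than its weakest sentence, and much of that stands.

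- **A reader might infer that safety reporting covers only people given exercise.** It does not. The SAE definition is unrestricted, relatedness in 10.4 extends to any research procedure, and all participants are asked about AEs at visits. A control's serious event during an exercise test falls within the SAE rule. It would also be too strong to say that the control arm can have no AEs. The defect is confined to the AE definition, and so to non-serious events under a literal reading.
- **A reader might infer that a sudden death would go unreported or escape all review.** It would not. It would be recorded on the CRF with severity and relatedness. Section 10.4 rests on the Chief Investigator's judgement and does not refer to section 10.7, whose table sits in a description of risks and is not labelled as the reference for expectedness. The Chief Investigator could report the death. What stands is narrower: the text permits a reading under which this report is not required.
- **A reader might multiply the protocol's rate by planned exposure.** At below 0.01 serious events per 10,000 hours, 100 people × 48 sessions × 70 to 90 minutes gives 5,600 to 7,200 hours and at most 0.0056 to 0.0072 events. It is tempting to conclude that one event, at over 100 times that count, cannot be called expected. This confuses two meanings: regulatory expectedness asks whether an event is foreseen for a procedure, and a foreseen complication can be very rare. The point does not rest on this figure.
- **The 18-month window is longer than follow-up.** It cuts off no data, and 10.2 supplies a usable end point. This part is minor.

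**Conclusion.** Three wording conflicts stand in the current protocol and should be fixed.

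1. The AE definition leaves out non-serious events in the 100 planned controls, and in both arms at baseline. It contradicts 10.3 and 10.4 and would bias a between-arm comparison of AEs.
2. The section 10.7 list can be read to exempt a training-related sudden death from the 15-working-day REC report, though not from CRF recording.
3. The safety window names a visit 24 to 26 weeks beyond the last one scheduled.

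The first consequence assumes that staff apply 10.1 as written and that AEs are compared by arm; the statistics chapter does not set out that analysis. The second assumes that the 10.7 list is used to judge expectedness, which the text neither requires nor rules out. Neither assumption is far-fetched, and plain wording would remove both.

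**What to change.** - **10.1:** define an AE as any untoward medical occurrence in any enrolled participant, in either arm, from baseline, so that it matches 10.3 and 10.4.
- **10.4 and 10.7:** state that the 10.7 table describes the risks of training and does not make a fatal or life-threatening related SAE expected for REC reporting.
- **10.2 and 10.4:** reconcile the 18-month window with the 52-week final visit, and use one end point in both sections.

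The cost is protocol wording, a few more AE entries from controls and baseline visits, and possibly a rare extra REC report. No new visits are needed, because participants are already asked about events at each one.

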## Cardiopulmonary Exercise Testing

Cardiopulmonary exercise testing is very safe and is even used in people with heart failure. However, as can occur with all forms of hard exercise, very occasionally some people have significant changes in their heart rate and rhythm that requires medical attention. Although the risk of this happening is small, the test is carried out in a room equipped with emergency monitoring, emergency medications and resuscitation equipment. Medical personnel will be available throughout the testing. Participants' heart rate and electrocardiography (ECG) are monitored throughout the exercise testing and if there are any concerns the exercise test will be stopped.

# STATISTICS AND ANALYSIS

## Description of Statistical Methods

The analysis will be carried out on the basis of intention-to-treat (ITT). This is, after randomisation, participants will be analysed according to their allocated intervention group irrespective of what they actually receive.

Patient demographic characteristics and other baseline information will be summarised by treatment group. Numbers (with percentages) for binary and categorical variables and mean (standard deviation), or median (interquartile or full range) for continuous variables will be presented. Normality of variables will be assessed by visual assessment of the normality curves and the Shapiro-Wilk test. The analysis of the primary outcome will be assessed using analysis of covariance (ANCOVA) adjusting for baseline values and minimisation factors used in the randomisation process. Results will be presented as adjusted mean difference in change in ambulatory blood pressure between randomised groups at 4 months with 95% confidence intervals (CI) and associated two-sided p value. The analysis of secondary outcomes will also be done using analysis of covariance (ANCOVA) to establish a co-variant model to examine the effect of cardiac structure, vascular function and lifestyle behaviours on exercise capacity. Outcomes measured on more than one occasion will be analysed using a mixed effects model. The data collected from the sub-study will be analysed using paired and independent T-test. If the model assumptions are not met and evidence of departure from Normality is observed, transformations of the data will be employed or non-parametric tests will be carried out. Statistical analysis will be carried out using STATA or SPSS statistical software.

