**The purpose of the TEPHRA blood cell and biomarker validation sub-study**

Hypertension affects 1 in 4 adults in the UK and increases the risk of cardiovascular diseases and stroke. It is caused by a multitude of factors. As part of an ongoing trial, TEPHRA study is a randomised controlled trial to determine whether modification of lifestyle through an exercise intervention can reduce heart and blood vessel risk in young adults. In the sub-study, healthy participants will undergo measurements of specific characteristics of blood cells and circulating factors in venous blood obtained from veins as part of protocol validation. It is crucial to validate how blood cells and circulating factors vary naturally from day to day in the same individual.

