| To investigate cardiac adaptation and remodelling following exercise intervention in preterm and full term born participants compared to non-exercising controls | Cardiac Echocardiography (all participants n=200)   - Cardiac Mass - Ventricular Structure and Function - 3D-shape and functional analysis   Cardiac MRI ( MRI subgroup n=100)   - Cardiac Mass - Ventricular Structure and Function - 3D-shape and functional analysis | Echocardiography completed at:  - baseline  - upon completion of 16 week intervention  - 52 weeks post randomisation (optional)  Cardiac MRI completed at:  - baseline  - upon completion of 16 week intervention |
| To investigate the change in microvascular structure and function post exercise intervention compared to control | Retinal Imaging  Dermal Capillaroscopy | Measured at:  - baseline  - upon completion of 16 week intervention |
| To investigate the degree of natural variability in circulating angiogenic, vascular and vasoactive markers and biomarkers in blood of the healthy volunteers | Blood analysis tests including but not limited to protein and gene-expression assays | Measured at:   - Sub-study baseline visit 1 - Sub-study visit 2 (1 week post visit 1) |
| To quantify mean changes in circulating angiogenic and vascular markers and biomarkers at rest and following peak exercise between intervention and control participants | Whole, plasma, and serum blood samples at rest and following peak exercise testing | Measured at:  - baseline  - upon completion of 16 week intervention  - 52 weeks post randomisation (resting only) |
| To investigate levels of vasoactive markers and biomarkers related to renal function at rest and following peak exercise between intervention and control participants | Whole, plasma, and serum blood samples at rest and following peak exercise testing | Measured at:  - baseline  - upon completion of 16 week intervention  - 52 weeks post randomisation (resting only) |
| To investigate neurophysiological remodelling following exercise intervention compared to control | Brain MRI (MRI subgroup n=100)   - Ventricular volume and shape - Presence of white matter lesions - White matter microstructural differences including fractional anisotropy - Vessel Density and Tortuosity   Gait analysis accelerometry profile | Measured at:  - baseline  - upon completion of 16 week intervention |

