# TRIAL DESIGN

**Summary of Study**

- Design and aims

The trial is an open, parallel arm randomised control trial which will investigate the effectiveness of physical activity behaviour change and structured exercise to lower blood pressure in young adults with pre-hypertension and Stage 1 hypertension. The results will be interpreted with specific reference to preterm vs full-term birth.

- Participant profile and recruitment.

Participants will be characterised as preterm (born before 37 weeks gestation, n=100) or full term (born after 37 weeks gestation, n=100). Participants will be aged from 18 to 35 years old, with a screening blood pressure above 120mmHg systolic and/or above 80 mmHg diastolic with systolic blood pressure not exceeding 160mmHg and diastolic blood pressure not exceeding 100mmHg. Recruitment will be driven from invitation from GP records, invitation from birth hospital birth registers, open recruitment, web-based recruitment, and participation in previous studies.

In total 200 participants will be recruited and randomised following baseline measures to exercise intervention (n=100 (includes 50 preterm)) or to a comparison control group with minimal intervention (n=100 (includes 50 preterm)).

We will test the reproducibility of our blood cell and circulating biomarkers by recruiting a cohort of healthy participants aged between 18 to 35 years old (n=20). The validation study is crucial to determine the reproducibility and evaluation of experimental protocols that is required for future publications including attempt to control the variability of time factor. Participants with a clinic blood pressure below 160mmHg systolic and 100mmHg diastolic blood pressure will be eligible for inclusion. Recruitment will be driven via poster advertisement.

Study visit and measures

Participants who enter the trial will nominally complete 4 study visits within the following 6 stages of the trial:

I. Screening assessment (Visit 0)

II. Baseline (Visit 1)

III. Randomisation and allocation to intervention or control

IV. 1^st^ follow-up (Visit 2) at 16 weeks (immediately post structured exercise intervention)

V. 2^nd^ follow-up (Visit 3) - (52 weeks post randomisation)

VI. Optional exit interview reporting participant experience.

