**Blood Cell and Biomarker Sub-Study:**

For a small sub-cohort, participants will have their clinic blood pressure measured at the first visit. Participants with blood pressure below 160mmHg systolic and 100mmHg diastolic will be included into the sub-study (n=20) for blood cell and biomarker validation, regardless of birth history.

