In children and adolescents, maintaining high cardiovascular fitness can be associated with between 5% and 10% difference in regional FA[^42^](#_ENREF_42). In older adults, the difference in regional FA between sedentary groups and those that maintain light to moderate activity is between 1 to 2%. With 100 participants in the MRI study, the intervention will be powered to 80% to report between 4% and 7% change between training and control groups.

*Small vessel tortuosity*

Maintaining higher cardiovascular fitness is associated with over a 15% difference in vessel tortuosity compared to lower fitness in older adults[^32^](#_ENREF_32). The study will be powered to 80% to detect 1% improvement in vessel tortuosity in the exercising participants with 100 participants completing MRI imaging (50 training).

Cerebrovascular Perfusion

Mersov et al in a modelling estimation of the sample size required to detect an arterial spin labelling magnetic resonance imaging perfusion abnormality in voxel-wise group analyses^52^ identified a requirement for a minimum of 22 participants for a 15% difference and 37 participants for a more modest 10% difference.

*Structural volumes*

Grey matter volumes are reduced in preterm born adolescents and young adults compared to full born controls. Mullen *et al* report preterm volumes of 659.3 cm3 (SD 52) compared to 700 cm3 (SD 51)[^42^](#_ENREF_42). This study will be powered to detect 6% improvement in preterm grey matter volumes equivalent to increasing volumes to mean values in the full term population

*Blood validation sub-study*

To validate methodology and assess variability a minimum number of 12 participants are needed as recommended for pilot investigations^53^.

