## Analysis of Outcome Measures

Descriptive statistics (mean, standard deviation, standard error, range, etc) will be calculated for each outcome for each group. Differences in the primary and secondary outcomes will be compared between intervention and control groups.

Mean changes in blood pressures and cardiovascular fitness will be compared across the population and correlated with cardiovascular endpoints including cardiac structure and function reported from cardiac MRI and echocardiogram.

Demographic and physiological characteristics of the participants will be added to regression models as covariates to explore the determinants of change in blood pressure comparing preterm and full term born participants.

Statistical analysis will be carried out using a computer software package, applying statistical methods to analyse dependent and independent variables within the study database. The variable will be plotted to categorize distribution and assess if the data is normally distributed which will guide the statistical methods. Methods such as the Student T-test will assess for differences between the groups and linear regression analysis will be used to assess if the study variables can explain differences in primary outcome. It is hoped that this will then allow for clear understanding on how the cardiovascular system adapts following exercise training and how remodelling may differ according to birth history and early life exposures. For the sub-study, the statistical analysis will be carried out using a computer software package and data will be analysed using paired and independent t-test. This will access the variability of circulating blood biomarkers within the same participant across both visits and also between each participant.

A detailed statistical analysis plan will be written with our statistical team and will be completed before receipt of the data.

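### The blood validation sub-study is meant to estimate variability, but the plan assigns it t-tests, which compare means, and does not say a within-person SD will be reported

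*Supplement*

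**What the plan says.** The purpose is stated consistently. Section 5 (Objectives and Outcome Measures) gives the sub-study objective as: "To investigate the degree of natural variability in circulating angiogenic, vascular and vasoactive markers and biomarkers in blood of the healthy volunteers". The background section on the sub-study adds: "It is crucial to validate how blood cells and circulating factors vary naturally from day to day in the same individual". The Summary of Study in section 6 calls the aim reproducibility: "We will test the reproducibility of our blood cell and circulating biomarkers by recruiting a cohort of healthy participants aged between 18 to 35 years". Section 7.1 describes a single cohort whose members "will be included into the sub-study (n=20) for blood cell and biomarker validation, regardless of birth history". Section 8.7 brings each person back exactly one week after the first sample, so there are two measurements per person.

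The analysis is named twice. Section 11.1: "The data collected from the sub-study will be analysed using paired and independent T-test". Section 11.3: "For the sub-study, the statistical analysis will be carried out using a computer software package and data will be analysed using paired and independent t-test". The sentence that follows in 11.3 says what this is expected to deliver: "This will access the variability of circulating blood biomarkers within the same participant across both visits and also between each participant".

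On size, section 11.2 says: "To validate methodology and assess variability a minimum number of 12 participants are needed as recommended for pilot investigations". For the sub-study, the protocol names no within-person SD or CV, ICC, limits of agreement or variance-components model.

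**The concern.** The objective asks how large the variation is, within a person and between people. Both are variances. The named methods test whether two means differ. Individual values can swing widely between visits, and if rises and falls cancel, the paired test sees nothing.

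For the variation between participants, the plan offers an independent t-test without saying which two groups it compares. Even with groups defined, a difference of two means is not a measure of spread among individuals.

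What is at stake is the sub-study's own result. Followed literally, the plan produces p-values on mean change and leaves its stated objective without a specified estimate.

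**Working it through.** **Inputs.** From the protocol: n = 20 planned, minimum 12, two visits one week apart, one cohort. The protocol gives no alpha, SD or effect size for the sub-study. Assumed for illustration: two-sided 5% level, between-person SD σb = 1, and within-person SD σw from 0.1 to 5.

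**The plan's own figure.** The minimum of 12 is a cited pilot-study recommendation. It comes with no alpha, power, effect or SD, so there is no calculation to reproduce.

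**Step 1: what the paired test responds to.** Let d be the visit 2 minus visit 1 difference. Its SD is σw√2, and the statistic is t = mean(d) / (SD(d)/√n). With no mean shift and normal errors, this follows a t distribution on n − 1 degrees of freedom whatever σw is. With a shift δ, the noncentrality is δ√n/(σw√2). For δ = 0.25 and n = 20 this is 0.25 × √20 / (√2 × σw) = 0.79/σw, which falls as the marker becomes noisier. ICC = σb²/(σb² + σw²). Simulation with 20,000 runs and n = 20 gave these rejection rates:

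| σw | ICC | Paired, no shift | Paired, shift 0.25 | Independent (visit 1 v visit 2), no shift |
|---|---|---|---|---|
| 0.1 | 0.99 | 5.2% | 100% | 0.0% |
| 0.5 | 0.80 | 5.1% | 32.2% | 0.0% |
| 1 | 0.50 | 4.8% | 11.6% | 0.6% |
| 2 | 0.20 | 4.8% | 6.1% | 2.8% |
| 5 | 0.04 | 4.9% | 5.2% | 4.5% |

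With no shift, the paired result is the same for a nearly perfect marker and a nearly unreproducible one. With a small shift, the least reproducible marker is the most likely to look unchanged.

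**Step 2: the independent test.** The last column shows one possible use, visit 1 against visit 2. The test takes the variance of the mean difference as 2(σb² + σw²)/n, whereas the true value is 2σw²/n. The ratio of true to assumed is 1 − ICC, which explains the rates near zero for reproducible markers. The protocol does not say the test would be used this way. It defines no groups at all.

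**Step 3: what the same data can deliver.** The within-person SD can be estimated as SD(d)/√2. Its 95% interval is the estimate multiplied by √(df/χ²) at the 97.5% and 2.5% quantiles.

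- n = 20, mean visit shift removed (df 19): √(19/32.85) = 0.76 to √(19/8.91) = 1.46.
- n = 12, mean visit shift removed (df 11): √(11/21.92) = 0.71 to √(11/3.82) = 1.70.
- No visit term: df 20 gives 0.77 to 1.44, and df 12 gives 0.72 to 1.65.

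For the one-way ICC with two measurements per person, the F-based 95% intervals (F = (1 + ICC)/(1 − ICC), with n − 1 and n degrees of freedom) are:

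| Assumed observed ICC | n = 20 | n = 12 |
|---|---|---|
| 0.5 | 0.09 to 0.77 | −0.05 to 0.82 |
| 0.8 | 0.57 to 0.92 | 0.46 to 0.94 |
| 0.9 | 0.77 to 0.96 | 0.70 to 0.97 |

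The design can therefore estimate the target, with moderate precision at n = 20.

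**The case against.** **The paired test contains the right quantity.** This stands. The SD of the differences is part of the calculation and, divided by √2, estimates the within-person SD. A reader might infer that the planned analysis carries no information on variability. That is true of the p-value, not of the data. The gap is that nothing says this SD will be reported or interpreted.

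**Other text covers it.** Section 11.1 has a general sentence assigning mixed models to repeatedly measured outcomes, but the next sentence gives the sub-study t-tests specifically. Section 11.3 promises means, SDs and ranges by group. These describe spread across people, not variation within a person. It also promises a detailed statistical analysis plan, which is not shown. Choosing a reliability index could fairly be left to that plan, but here the protocol has already named a method, twice, that does not fit the aim.

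**The independent test might have a use.** Section 7.4 admits both sexes and both preterm and full-term births, so a two-group comparison is possible. The protocol specifies none, and section 7.1 enrols without regard to birth history. The fair criticism is that the comparison is undefined. It would go too far to say that no valid use exists, or that the test will be applied to the two visits.

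**Consequences a reader might add.** One could infer that a non-significant result will be read as proof of reproducibility, or that the main trial's biomarker analysis depends on this SD. The protocol says neither. It gives protocol validation and reproducibility for later publications as the reasons for the sub-study, and the main-trial biomarker objectives compare randomised arms without taking this SD as an input.

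**Conclusion.** The point holds, at moderate severity. Sections 11.1 and 11.3 name tests of means for an objective about variances, and 11.3 says outright that those tests will assess variability. With no mean shift, the paired p-value is about 95% likely to be non-significant at any within-person SD. The independent test has no defined comparison and does not measure variation between participants.

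The problem is confined to the 20-person sub-study. It does not affect the randomised comparison, the blood pressure outcomes or the trial's sample size, and the planned samples are enough to produce the right estimate.

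The simulated rates assume normal errors and the illustrative SDs above. The flat 5% rate with no shift does not depend on which SDs are chosen. The interval factors also assume normality, possibly after a log transformation. Because the samples are one week apart, what is estimated is one-week variation, although the background text speaks of daily variation.

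**What to change.** In sections 11.1 and 11.3, replace the t-tests as the main sub-study analysis with wording such as: each marker, log-transformed where skewed, will be analysed with a random-effects (variance-components) model with participant as a random effect; the within-person SD or CV over one week, the between-person SD and the ICC will be reported with 95% confidence intervals. Keep the paired mean difference only as a check for systematic drift between visits, and add a visit term if drift is present. Delete the independent t-test, or state which groups it compares and why.

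A repeatability coefficient and limits of agreement may be added, but with two visits they largely restate the within-person SD. Carry the same wording into the statistical analysis plan.

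The cost is about two sentences in the protocol, with no new samples, visits or staff.
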